### Data Analysis

The Biomedical Statistics and Data Science Lab also collaborates with the CRHC-DC to conceptualize and implement statistical analysis plans and facilitates interpretation of results. The Strengthening the Reporting of Observational Studies in Epidemiology (STROBE) statement (63) for observational studies and the Methodology Standards developed by the Patient-Centered Outcomes Research Institute (64) (including all cross-cutting standards) were employed in the design of the study.

For each research question, the team will develop a causal diagram (65) for the exposure-outcome relationships of interest, including a list of the predictors, confounders, mediators (i.e., measures on the causal pathway between the exposure and outcome), and potential effect modifiers of the exposure-outcome relationship. The causal diagram will be used to specify standard regression models, including linear regression for continuous outcomes, logistic regression for binary outcomes, Poisson or negative binomial regression (depending on the skewness of the outcome distribution) for counts and rates, and mixed models with a random intercept (in combination with the previously-specified types of regression models) to account for within-subject correlation (66). The included variables and their parameterization in the model (e.g., interactions or non-linear terms) are guided by clinical knowledge of the hypothesized relationship from the causal graphs. In cases where the clinical importance of a variable or subset of variables is unclear to investigators, significance tests (e.g., partial *F*-tests or likelihood ratio tests) will be used to assess significance against the reduced model (i.e., terms deemed a-priori as clinically important). In some cases, the number of variables and complexity of the model may be limited by the available sample size.

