**Methods and Analysis:**

TPS is rooted in community-partnered participatory research (CPPR), health equity, antiracism, and developmental science. Using our community-informed conceptual framework of child thriving, the THRIVE Study will assess cross-cutting measures of place, environment, health service use, and other social determinants of health to provide longitudinal associations with developmentally appropriate child and youth thriving outcomes across participants in six cohorts spanning from pregnancy through adolescence (child ages 0-18 years). Data from electronic health records, school records, and health and human services use are integrated to assess biological and social influences of thriving. We will examine changes over time using paired *t*-tests and adjusted linear regression models for continuous thriving scores and McNemar tests and adjusted logistic regression models for categorical outcomes (thriving/not thriving). Data analyses will include mixed models with a random intercept (in combination with the previously-specified types of regression models) to account for within-subject correlation.

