#### Primary Research Objectives

The overarching study objectives are:

To determine the key biological, psychological, social, community/neighborhood, environmental factors that influence child and youth thriving outcomes across childhood.To identify the effect of policies and place-based factors on childhood thriving through community-partnered and equity-focused policy analysis and outreach.

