These inequities in important social influences on health drive many of the health and academic disparities in child health observed in Allegheny County. For example, infant mortality rates vary by race from 14.1 deaths per 1,000 live births for Black infants compared to 3.3 deaths per 1,000 live births for White infants (24). Two times as many Black infants were born with low birth weight in 2018 relative to White infants (13.9 vs. 6.2%), and asthma hospitalization rates were over four times higher among Black children than White children in 2018 (25). Complete childhood immunization rates were lower among Black 18-35 month old toddlers compared with White toddlers (55 vs. 68%) (26). According to the 2019 Inequality Across Gender and Race report about the city of Pittsburgh (27), Pittsburgh's high schools are in the bottom 20% for students taking ACT/SATs, and White residents are three times more likely to have a college degree than Black residents. While high school graduation rates are high, 16% of Black men in Pittsburgh do not have a high school diploma or GED, 2.5 times higher than White residents (27).

Given these persisting inequities, the Pittsburgh Study team brings together groups committed to child health through research and community action. TPS THRIVE is a longitudinal, prospective, observational study that collects cross-cutting child, caregiver, household, and community measures that will follow children over time from birth through high school. THRIVE will enroll participants who are part of the cohort intervention studies as well as siblings and other eligible children in Allegheny County, which is located in Southwestern PA and includes Pittsburgh and its surrounding communities. This approach functions similarly to an accelerated longitudinal cohort design to provide more rapid results and allow earlier translation into practice of effective interventions and guidance for child and adolescent-relevant policies. TPS THRIVE will enroll participants from six cohorts—pregnancy, early childhood, early school-age, middle childhood, and adolescence (middle school and high school), as shown in Figure 2 (TPS Study Design) and described in more detail below.

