#### Subgroup Analyses

Given the focus of TPS on building health equity in child outcomes, we will conduct subgroup analyses by child race/ethnicity, child gender identity, and family income level to determine any differential access to programs. Both unadjusted and adjusted analyses will be performed. Adjusted analyses will include key demographic variables and other variables identified as potential confounders of the relationship between the exposure and outcome measures.

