### Strengths and Limitations

Strengths of TPS THRIVE include its grounding in a comprehensive, community-informed conceptualization of childhood thriving and its asset-based approaches in building on the strengths of families and neighborhoods in supporting childhood thriving. This transdisciplinary collaboration integrates experts in pediatrics, developmental science, education, health services research, community health, public health, social work, biostatistics, epidemiology, behavioral health, engineering, and biological and environmental science along with community organizations in an innovative community-partnered research model. By integrating community organizations and members, this study builds on positive practices already present in our community, identifying interventions that have community relevance and contextual validity.

Limitations of this study include self-report bias of survey data, selection bias, and lack of randomized, control groups for some of the cohort intervention studies. Secondary data and direct assessments will be used when available to supplement self-reported survey data. Propensity score matching to account for group differences will be used when randomized comparison groups are unavailable. Different sample inclusion/exclusion criteria may make it difficult to compare children across cohorts over time.

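### Split each time-varying factor into a child-mean and a within-child term, so that one blended random-intercept coefficient is not read as the effect of a change in the factor

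*Protocol article*

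**What the plan says.** The first of the Primary Research Objectives is "To determine the key biological, psychological, social, community/neighborhood, environmental factors that influence child and youth thriving outcomes across childhood". The abstract states the aim more softly: "to provide longitudinal associations with developmentally appropriate child and youth thriving outcomes". Under Study Design and Setting the study is described as longitudinal, prospective and observational.

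The Data Analysis section draws a causal diagram for each research question and uses it to specify linear, logistic or count regressions. For the repeated assessments it adds "mixed models with a random intercept (in combination with the previously-specified types of regression models) to account for within-subject correlation". Accounting for correlation is the only job given to the random intercept.

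On how factors enter the model, the section says: "The included variables and their parameterization in the model (e.g., interactions or non-linear terms) are guided by clinical knowledge of the hypothesized relationship". Adjustment, under Subgroup Analyses, covers key demographic variables and "other variables identified as potential confounders of the relationship between the exposure and outcome measures". Strengths and Limitations names self-report bias and selection bias, but not stable unmeasured confounding. The article nowhere mentions a child-mean term, fixed effects, or the condition that the random intercept be unrelated to the exposures. Nor does it say that each factor enters as a single term.

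**The concern.** Many measures in Table 2 can change between annual assessments: caregiver stress, food security, sleep, perceived neighborhood safety, social support. Entered as an ordinary term in a random-intercept model, such a factor has one coefficient. That coefficient pools two comparisons: children with habitually higher values against children with lower ones, and the same child at higher and lower values. It estimates the within-child association only if the child's intercept is uncorrelated with the factor, given the adjustment variables.

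Measured confounders are handled by the causal diagram. Stable unmeasured differences between families or places stay in the intercept, and where they are correlated with the factor they load onto its coefficient. A factor that only marks such differences could then be reported as one that influences thriving, and results are meant to guide interventions and policy (Implications). The repeated assessments can separate the two comparisons, but the article does not say that they will be used for this.

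**Working it through.** **The plan's own figures.** Sample Size gives 4,930 × 0.50 × 0.85 = 2,095 children aged 6 to 18 and 7,500 × 0.50 × 0.85 = 3,187 aged 0 to 5, each with two annual assessments. Both reproduce. Alpha is 0.05 (sidedness not stated; two-sided used), and the Brief Inventory of Thriving (BIT) SD is 0.78. The article gives no error rate for the mixed model, no ICC and no size of residual confounding.

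**Assumptions.** Continuous outcome, T = 2 assessments, exposure and outcome in SD units, outcome ICC c_y = 0.5, exposure ICC c_x = 0.3, 0.5 or 0.7, true within-child effect 0. Let r be the correlation, left after adjustment, between the stable part of the exposure and the child's stable outcome level.

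**Formulas** (information per child):
- within-child: W = (T − 1)(1 − c_x)/(1 − c_y)
- between-child: B = T·v/[(1 − c_y) + T·c_y], with v = c_x + (1 − c_x)/T
- between-child slope when the within-child effect is 0: r·√(c_x·c_y)/v
- blended coefficient: [B/(W + B)] × between-child slope
- standard error: 1/√[N(W + B)]

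**One case in full** (c_x = 0.5, r = 0.1, N = 2,095):
- W = 0.5/0.5 = 1; v = 0.75; B = 1.5/1.5 = 1, so each part has half the weight.
- Between-child slope = 0.1 × 0.5/0.75 = 0.0667; blended coefficient = 0.0333.
- Standard error = 1/√4,190 = 0.0154; z = 2.16; rejection = Φ(2.16 − 1.96) = 58%.
- On the BIT scale the false coefficient is 0.0333 × 0.78 = 0.026 per SD of exposure.
- At r = 0.02, z = 0.43 and rejection is about 7%.

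**Simulation**, 1,000 data sets per cell, two assessments, N = 2,095. Entries are the percentage rejecting a true null within-child effect, single-term random-intercept model:

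| r | c_x = 0.3 | c_x = 0.5 | c_x = 0.7 |
|---|---|---|---|
| 0 | 3.5 | 5.2 | 3.9 |
| 0.05 | 11.6 | 21.1 | 30.1 |
| 0.1 | 34.1 | 56.2 | 76.7 |
| 0.2 | 89.8 | 99.3 | 100 |

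The within-child estimate, which is the coefficient obtained once the child's mean is added, rejected 4 to 7% in every two-assessment cell.

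**More assessments** (c_x = 0.5, r = 0.1, N = 2,095, 300 data sets per cell): 43% with five and 24% with ten.

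**Price of the split** (c_x = 0.5, r = 0, true effect 0.05 outcome SD per exposure SD, N = 2,095): the blended coefficient has z = 0.05/0.0154 = 3.24 and power 90%. The within-child coefficient has standard error 1/√2,095 = 0.0218, z = 2.29 and power 63%; simulation gave about 60%.

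**The case against.** The strongest reply is that nothing stated is wrong. The random intercept is there for within-subject correlation, and it serves that purpose. Parameterization is left to the causal diagrams, and a child-mean term fits inside the stated model. A reader might infer that the article commits itself to one coefficient per time-varying factor. It does not; that is only the default reading of a random intercept with ordinary covariates. This part of the reply stands.

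It also stands that the size is assumed. A reader might infer that the test rejects far above 5% as a matter of course. The documents do not support that: they give no r, the level holds at r = 0, and at r = 0.02 it is about 7%. Two assessments are the basis of the sample size, but follow-up is planned from birth through high school, and more assessments weaken the effect. A reversed sign is possible (a true effect of −0.05 with r = 0.2 gives −0.05 + 0.0667 = +0.017), but only in a chosen scenario.

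The reply is also right that the choice of estimand is a trade-off. The first objective covers community and neighborhood factors as well, and much of that contrast lies between children. Making the within-child coefficient its only answer would discard this contrast and cost power. As a plain association, the blended coefficient is not a false positive. The simulated figures also do not describe the 0 to 5 primary outcome, which Sample Size treats as a prevalence. Nor does it follow that the study gains little over a cross-sectional survey, since paired analyses of change are planned too.

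The reply does not remove the mismatch between the default reading of the named model and an objective worded as influence. Reporting both coefficients resolves it without giving up the between-child information.

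**Conclusion.** This is a cheap improvement to the stated method, not an error in the plan. It applies to factors that vary within a child, entered as single terms, when the coefficient is read as the effect of a change in the factor. Under the assumptions above, the chance of rejecting a true null within-child effect at N = 2,095 is about 5% with no residual stable correlation, 12 to 30% at r = 0.05 and 34 to 77% at r = 0.1. The mechanism follows from the model. The size depends on r and the ICCs, which the documents do not give, and on the number of assessments. The figures hold for a continuous outcome only.

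**What to change.** In the Data Analysis section, add that each factor measured at more than one assessment and varying within a child will enter as two terms, the child's own mean and the deviation from that mean, with the random intercept kept. Report both coefficients, labelled within-child and between-child, and state that a single blended coefficient will not be read as the effect of a change in the factor. Factors that vary little or not at all get the between-child coefficient only. For the binary 0 to 5 outcome, put the child-mean term into the random-intercept logistic model.

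The cost is one added covariate per such factor and a sentence or two of text; no new data are needed. The within-child coefficient has wider intervals (about 60% against 90% power in the case shown, without stable confounding). It also remains open to time-varying confounding and reverse causation, which the text should say.

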*Adolescent—Middle School:* The Adolescent—Middle School Cohort (grades 7 and 8) features a middle school study examining the effectiveness of Expect Respect, a teen dating violence and sexual violence prevention program, for middle school age adolescents with histories of exposure to trauma and violence. The two-arm cluster randomized controlled trial in 36 middle schools from local public-school districts and charter school networks will compare violence and bystander behaviors between schools receiving Expect Respect trauma-sensitive support groups compared to schools receiving individual enhanced care assessments.

*Adolescent—High School:* The Adolescent—High School Cohort (ages 13-19) incorporates a community-partnered two-arm cluster randomized trial set in 24 neighborhoods in Allegheny County with concentrated disadvantage to examine the effectiveness of Creating Peace, a trauma-focused, gender-transformative youth violence prevention program that integrates racism and discrimination prevention compared to job readiness training.

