### Study Participants

#### Inclusion and Exclusion Criteria

Study eligibility criteria are parents and caregivers who are pregnant or have a child 0-18 years old living with them who reside in Allegheny County, PA. Multiple children per family may enroll in the study between ages 0-18 years old. Children and youth will participate in completing surveys themselves starting at age 8 years old. Currently, the study is open to participants who speak English and Spanish.

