#### Recruitment Strategy

Families enrolled in all TPS cohorts are invited to participate in the TPS THRIVE Study. Each of the TPS age cohorts have tailored recruitment strategies based on sample size, intervention site, and intervention delivery. Collaboratives partnered with multiple organizations to recruit pregnant women, new mothers at maternity hospital sites, Special Supplemental Nutrition Program for Women, Infants, and Children (WIC) offices, Federally Qualified Health Centers (FQHCs), and pediatric primary care offices throughout the region. School-based studies recruit families of students enrolled in participating schools and community organizations.

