### Study Comparison Groups

TPS combines family, school, and neighborhood-level interventions, targeting contexts most relevant to improving child outcomes by developmental age. For baseline survey data, descriptive analyses will assess mean levels of outcomes across subgroups (by age, sex, race/ethnicity, and family income). We will examine changes over time using paired *t*-tests and adjusted linear regression models for continuous outcomes and McNemar tests and adjusted logistic regression models for categorical variables.

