### Data Management

#### Data Entry and Tracking

The Center for Research on Health Care Data Center (CRHC-DC) serves as the Data Core for TPS. The Data Core develops strategies for study data entry and management. Data are entered electronically via a password-protected web-based data entry system, but paper versions of forms are provided for manual entry in case of technical problems. Our web-based system, developed using ASP.NET programming, adheres to guidelines set by FDA 21 CFR Part 11, which mandates practices with respect to data access, data confidentiality, password protection, audit trails, validation, and direct data entry. The data entry process begins during the online participant registration into TPS which generates a participant ID at initiation to track participants, link data, and maintain data confidentiality. The tracking system produces a schedule of data collection for each participant. TPS study coordinators log into the data entry and tracking system, enter the participant's study ID, and choose the visit to be viewed. The appropriate set of forms are generated for that participant based on the visit number. To minimize missing data, all study forms have certain key fields that are required before forms can be submitted. The web-based system can link each TPS study participant across multiple cohorts and across multiple family members.

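### The models allow only for within-child correlation, although siblings enrol and part of the sample comes through schools and neighborhoods, so standard errors will be too small for household-, school- and place-level exposures.

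*Protocol article*

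**What the plan says.** Data Analysis lists linear, logistic and Poisson or negative binomial regression, and then "mixed models with a random intercept (in combination with the previously-specified types of regression models) to account for within-subject correlation". The abstract repeats this purpose. Study Comparison Groups adds: "We will examine changes over time using paired *t*-tests and adjusted linear regression models for continuous outcomes", with McNemar tests and logistic regression for categorical variables. None of these carries a family, school or neighborhood term.

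The design groups children in several ways:

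- **Families.** Inclusion and Exclusion Criteria: "Multiple children per family may enroll in the study between ages 0-18 years old". Study Design and Setting: "THRIVE will enroll participants who are part of the cohort intervention studies as well as siblings and other eligible children in Allegheny County".
- **Schools and community sites.** Recruitment Strategy: "School-based studies recruit families of students enrolled in participating schools and community organizations".
- **Clusters in feeder cohorts.** The middle-school cohort is a "two-arm cluster randomized controlled trial in 36 middle schools from local public-school districts" and charter networks. The high-school cohort is cluster randomized in 24 neighborhoods.

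A primary objective is "To identify the effect of policies and place-based factors on childhood thriving". Under Data Entry and Tracking, "The web-based system can link each TPS study participant across multiple cohorts and across multiple family members", but no stated analysis uses that link.

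Sample Size gives detectable differences at 85% power and alpha 0.05: 0.08 in parent Brief Inventory of Thriving (BIT) score and 5.5% in child flourishing with 3,187 children aged 0-5, and 1 point in youth BIT (SD 0.78) with 2,095 children aged 6-18. It gives no ICC, cluster size or design effect.

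**The concern.** A random intercept for the child absorbs correlation between repeated measurements of that child. It does nothing for correlation between two siblings, or between children in one school or neighborhood. When the exposure is shared by the whole cluster, the effective sample for that exposure lies closer to the number of clusters than to the number of children, and a model that counts children as independent reports too much precision.

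Such exposures are central here. Table 2 includes housing quality, water safety, food security and caregiver stress, which siblings in one household largely share. Family income is a planned subgroup variable. Objective 2 concerns place and policy, and Objective 1 includes community, neighborhood and environmental factors. The results are meant to guide interventions and policy, so an excess of false-positive findings on these factors would matter.

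**Working it through.** **1. Reproduce the plan's counts.** 7,500 × 0.50 × 0.85 = 3,187.5 and 4,930 × 0.50 × 0.85 = 2,095.25. Both agree with Sample Size.

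**2. Reproduce the detectable differences under independence.** Assume two equal groups and two-sided alpha (sidedness is not stated): MDD = (1.960 + 1.036) × SD × √(4/N).

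- *Parent BIT, N = 3,187.* The article gives SD 0.78 only for youth; apply it to parents as an assumption. 2.996 × 0.78 × √(4/3,187) = 0.0828, which rounds to the stated 0.08. Exactly 0.08 would have 82.5% power. With this SD there is no allowance for clustering.
- *Flourishing, N = 3,187.* No baseline prevalence is given. The MDD is 4.97 points at 30% and about 5.3 points near 50%. The stated 5.5 can therefore absorb a design effect of (5.5/4.97)² ≈ 1.22 at 30%, or (5.5/5.306)² ≈ 1.07 near 50%.
- *Youth BIT, N = 2,095.* On the mean-score scale the MDD is 0.102. A literal 1 point with SD 0.78 needs only 22 children, and its power stays at or above 85% up to a design effect of 2,095 / [4 × (2.996 × 0.78)²] ≈ 96.

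**3. Design effect for an exposure constant within the cluster.** DE = 1 + (m − 1) × ICC, with m children per cluster; true type I error = 2 × [1 − Φ(1.96/√DE)]. All m and ICC values are assumptions, except that m ≈ 35 is 2,095/60, the average if every 6-18 child came from the 36 schools and 24 neighborhoods.

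| Setting | m | ICC | DE | Type I error |
|---|---|---|---|---|
| Siblings, low | 1.3 | 0.3 | 1.09 | about 6% |
| Siblings, high | 1.5 | 0.5 | 1.25 | about 8% |
| School or neighborhood, low | 35 | 0.01 | 1.34 | about 9% |
| School or neighborhood, high | 35 | 0.05 | 2.70 | about 23% |

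Power for an effect set at 85% under independence falls to 81.9%, 76.4%, 73.5% and 44.6% respectively.

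**4. Check by simulation.** The setting was 150 families of two siblings, two waves, variance shares of 0.3 family, 0.3 child and 0.4 residual, a family-level exposure with no effect, and a child-only random intercept. It rejected in 11% of 200 runs at nominal 5%. The formula agrees: a child's two-wave mean has variance 0.3 + 0.3 + 0.2 = 0.8, the sibling correlation is 0.3/0.8 = 0.375, DE = 1.375, and expected type I error is 9.5%. The Monte Carlo standard error is √(0.11 × 0.89/200) ≈ 2.2 points.

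**5. Effect on the stated differences, ages 0-5.**

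- *Parent BIT, sibling range of step 3.* 0.0828 × √1.09 = 0.086 and 0.0828 × √1.25 = 0.093.
- *Parent BIT, siblings sharing one caregiver's score.* The calculation counts children, but the score is the parent's. For siblings with the same responding caregiver the ICC is 1, so m = 1.3 to 1.5 gives DE 1.3 to 1.5, and 0.08 becomes 0.08 × √1.3 = 0.091 to 0.08 × √1.5 = 0.098.
- *Flourishing.* At DE 1.25 the MDD is 4.97 × √1.25 = 5.6 to 5.306 × √1.25 = 5.9 points. At DE 1.09 it is 5.2 to 5.5.

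**The case against.** The strongest reply is that this is a condensed article. It says that models are built for each research question from a causal diagram and refers to statistical analysis plans, and the data system already links family members. A full plan may well name further cluster terms. That lowers the severity but does not remove the point, because the text states what the random intercept is for, and that purpose is within-subject correlation only.

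Other objections stand and set the limits:

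- **Scope.** Understatement applies to exposures that vary between clusters. Paired *t* and McNemar tests use change within a child, where stable family effects cancel, so the error rates above do not carry over to them. Demoting those tests to descriptive use would do nothing about clustering.
- **Parent SD.** Under independence 0.08 corresponds to SD 0.754. A parent SD of 0.70 would leave room for a design effect of (0.754/0.70)² ≈ 1.16.
- **Siblings in the power frame.** Sample Size is split into ages 0-5 and 6-18 and does not say whether siblings are counted. Only siblings in the same band inflate either calculation.
- **Cluster sizes.** The two cluster-randomized trials are separate intervention studies, and the 6-18 sample also draws on the kindergarten-to-grade-6 cohorts. A reader might infer 60 children in each of the 60 clusters, which with ICC 0.05 gives type I error of about 32%. That would need 3,600 children, against 2,095 in the whole 6-18 sample.

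**Conclusion.** The point holds for exposures that are constant or strongly correlated within a household, school or neighborhood. Analysed as written, these will have standard errors that are too small. Type I error would be about 6% to 8% from siblings and about 9% to 23% from schools or neighborhoods. These ranges rest on assumed ICCs and cluster sizes and on an exposure fully shared within the cluster; a partly shared exposure would be affected less.

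A reader might infer that every confidence interval is too narrow and every stated detectable difference too small. The documents do not support that. Exposures that vary within families or schools need not be affected. The 0.08 figure leaves no room for clustering if the youth SD of 0.78 applies to parents, and it counts children for a score that siblings may share. The 5.5-point figure is optimistic only for design effects above about 1.07 to 1.22, depending on prevalence. The literal 1-point youth figure is not threatened by clustering; setting it beside a mean-score SD of 0.78 raises a separate question of scale.

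This should be corrected before analysis, but the sibling effect is modest and the remedy is mostly wording.

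**What to change.** In Data Analysis, add a random intercept for family, with child nested within it. Add one for school or neighborhood where children are recruited that way or the exposure is measured at that level. Cluster-robust standard errors at the highest relevant level are an acceptable alternative.

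In Sample Size, state the assumed ICCs, children per family and children per school or neighborhood. Give the SD used for parent BIT, and say whether parents or children are counted. Restate 0.08 multiplied by √DE. State the baseline prevalence for flourishing and, where the design effect exceeds the slack in 5.5 points, restate that figure by multiplying its independence value by √DE.

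The paired *t* and McNemar tests need no change on this account.

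The cost is wording and a short recalculation, since family links already exist in the data system. The downside is wider intervals and slightly less favourable detectable differences.
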